### Additional consent provisions for collection and use of participant data and biological specimens {26b}

No additional data or biological specimens will be obtained.

## Interventions

### Explanation for the choice of comparators {6b}

The control group is treated according to usual care within an ERAS concept. Patients in the control group are assessed through some of the instruments that are used for the intervention group. These measurements are conducted by the regular ward staff (in general a nurse working at the surgery ward/outpatient clinic) at admission to hospital prior to surgery and at the postoperative outpatient visit (Table 2). These extra measurements are the only differences between the control group and patients not included in the trial.

### Intervention description {11a}

#### Standard protocol

Standard protocol for the treatment of colorectal cancer patients is according to best known practice, based on Swedish colorectal guidelines and within an ERAS setting. The preoperative investigation includes colonoscopy with biopsy (if possible), sometimes in combination with CT colonography, CT scans of the thorax and abdomen and in the case of rectal cancer also MRI of the lower abdomen. Each patient is thereafter discussed at a multidisciplinary team conference (MDT) and given a recommendation of treatment based on the endoscopic, radiologic and histopathologic findings. If the recommendation is surgery with a curative intent, this is scheduled within 4 weeks from their first visit at the outpatient clinic. According to the Swedish standardized referral pathways for colorectal cancer [36], the aim is to proceed from suspicion of colorectal cancer to surgery within 39 days. During this time, each patient has another appointment with the surgeon, followed by a pre-anaesthetic assessment by an anaesthesiologist. Interdisciplinary referrals (e.g. to cardiologist, lung physician) and/or further radiologic and physiologic examinations (e.g. UCG, spirometry) are made if deemed necessary through these evaluations. The patients are admitted to the surgical ward on the day before the planned surgery or the day of the operation. All surgical specimens are analysed by a pathologist and the postoperative TNM stage is determined. When the postoperative staging is completed, all patients are again discussed at MDT and a recommendation is made regarding following oncological treatment and future follow-up. All patients have a scheduled visit at the outpatient clinic in approximately 2 months post-surgery, to receive pTNM information, evaluate the postoperative recovery and plan for any following treatment and follow-up.

#### Intervention group

The patients in the intervention group receive standard care according to the description above but with the CGA and care intervention in addition. As soon as a patient has been randomized to the intervention group, they are scheduled for an “intervention day”, which takes place on pre-decided dates (once every week). During this day, each patient has an individual meeting with an internal medicine physician with geriatric profiling, a study nurse, a physiotherapist or occupational therapist and a dietician. The team conducting the screenings receives introduction about the intervention and education regarding the CGA concept prior to entering the study, and they are also able to address the local expertise of CGA if questions arise during the evaluations. Each profession evaluates the patient clinically and according to the determined screening tools and issues an individual action plan based on these results (Fig. 1). The recommendations are individually prescribed and based on the health care professional’s evaluations based on the standardized screening, according to the CRF. The instruments used by each profession at different measurement points are stated below (Table 1).

**Fig. 1 Fig1:**
[figure not shown]
Description of the CGA and care concept in the study

**Table 1 Tab1:** Screening instruments and assessments used for the intervention group, at baseline, at post-op visit (approximately 2 months post-op) and at 12 months post-op

Health care professional	Outcome and instruments	Other evaluations	Time of measurements
Internal medicine physician	- **Comorbidity**—*Charlson comorbidity index (CCI)* - **Medication safety**	- Review of SMA and current medications - Overall assessment of physiological status (including blood pressure and ECG)	**CCI** - Baseline - Post-op visit
Study nurse	- **Frailty**—*CFS-9* - **HRQoL**—*EQ-5D-5L* - **Cognition**—*MMSE* - **Medication safety**—*SMA and list of medications* -** Complications**—*Clavien-Dindo scale*		**CFS-9** - Baseline - Post-op visit **EQ-5D-5L** - Baseline - Post-op visit - 12 months post-op **MMSE** - Baseline **SMA** and list of medications - Baseline - Post-op visit **ADL** - Post-op visit **Complications** - Post-op visit
Physiotherapist	- **Dependence**—*ADL-step* - **Physical function** *hand grip strength (HGS) and six-minute walk test (6MWT)*	Overall assessment of the physical status	**ADL** - Baseline **HGS** - Baseline **6MWT** - Baseline
Dietician	- **Nutrition**—*MNA-SF*	Overall assessment of the nutritional status	**MNA-SF** - Baseline - Day of/day before surgery

All patients in the intervention group are discussed weekly in a group consisting of at least one representative from each profession. During these weekly meetings, the expected benefit of the interventions is weighed against the risk of delaying the surgery in each individual case. Adherence to the individually prescribed recommendations is evaluated and when the intervention is completed, or the patient for any given reason is not able to follow the recommendations, the intervention is terminated. To allow the CGA and care intervention to reach as much effect as possible, we have argued the need of, in some cases, allowing the time from diagnosis to surgery to be somewhat prolonged. In general, that time frame is 2–6 weeks but may in the trial setting be extended for up to 8 weeks. The overall objective is though, as in conventional care, to prepare the patient as quickly as possible for surgery without taking unnecessary medical risks. The postoperative phase is similar in both groups (Fig. 1).

#### Control group

The patients in the control group are assessed using some of the instruments that are used for the intervention group. These measurements are conducted by the regular ward staff (in general a nurse working at the surgery ward/outpatient clinic) at admission to hospital prior to surgery and at the postoperative outpatient visit (Table 2). These extra measurements are the only differences between the control group and patients not included in the trial treated according to standard protocol.

**Table 2 Tab2:** Screening instruments used for the control group, at baseline, at post-op visit (approximately 2 months post-op) and at 12 months post-op

Health care professional	Outcome and instruments	Time of measurements
Ward nurse/nurse at the outpatient clinic	- **Frailty**—*CFS-9* - **HRQoL**—*EQ*-5D-5L - **Cognition**—*MiniMental State Examination (MMSE)* - **Medication safety**—*Safe Medication Assessment (SMA) and list of medications* -** Dependence**—*Activities of Daily Living (ADL-step)* - **Nutrition**—*Mini-Nutritional Assessment-Short Form (MNA-SF)*	**CFS-9** - Baseline - Post-op visit **EQ-5D-5L** - Baseline - Post-op visit - 12 months post-op **MMSE** - Baseline **SMA** and list of medications - Baseline - Post-op visit **ADL** - Baseline - Post-op visit **MNA-SF** - Baseline - Day of/day before surgery
Member of the project steering groups	- **Complications**—*Clavien-Dindo scale* - **Comorbidity**—*Charlson comorbidity index (CCI)*	**Complications** - Post-op visit **CCI** - Baseline - Post-op visit

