#### Comprehensive geriatric assessment and care

The team conducting the CGA and care intervention in the trial consists of internal medicine physicians with geriatric profiling, study nurses, physiotherapists (and/or occupational therapists) and dieticians. The team works in close contact with the colorectal surgeons at the clinic. During the day of interventions, each patient is individually assessed by one member of each profession (Fig. 1).

The multimodal concept of comprehensive geriatric assessment and care is considered best practice when treating frail elderly patients [30, 37]. The multiprofessional and team-based examinations and assessments of the elderly individual identify both problems and resources in the elderly population and the assessments should lay the grounds for recommended treatment and follow-up. The use of CGA enables underlying unidentified conditions and problems to be identified and, if needed, specifically targeted, optimized and treated [38, 39]. Considering sarcopenia and nutritional problems being highly present amongst the frail elderly, physiotherapists (and/or occupational therapists) and dieticians are important members of the CGA and care team. A geriatric assessment, especially with a focus on medications, including risks of polypharmacy, inappropriate medications and ADRs, is also crucial [30, 40, 41].

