#### Outcomes and measurements

*Hospital stays and discharge destination*, data regarding the length of hospital stay, total number of hospital days within 3 months after discharge, discharge destination and use of home help services and 30-day readmission rates for all participants is collected from patient medical records.*Dependence*, evaluation of the level of independence/dependence in an elderly individual is of great importance for example when establishing the need of home help services or other assistance. This is assessed using the activities of daily living (ADL)-staircase, which is a validated and commonly used instrument. The screening results in a score from 0 to 9, where 0 is completely independent and 9 is completely dependent [42, 43]. A clinically significant change is defined as a change of minimum 1 step in any direction on the ADL-staircase. ADL-function is assessed at baseline and at post-op visit (approximately 2 months post-surgery). The patients are assessed by a physiotherapist or a study nurse at baseline and follow-up.*Physical function*, the physiotherapists are also using hand grip strength (HGS) and six-minute walk test (6MWT) to make an overall assessment of the patient’s physical status to establish individual recommendations on physical activity and exercise. Both HGS and 6MWT have previously been used in assessments of frail elderly patients [44, 45]. The tests are performed at baseline and not at follow-up and are only conducted on patients in the intervention group as part of the CGA and care intervention.*Nutrition*, malnutrition is common in the elderly population, especially if hospitalized, living in nursing facility or having home help services. Malnutrition is often unrecognized if not specifically targeted. The Mini-Nutritional Assessment-Short Form (MNA-SF) is a validated instrument for nutritional screening in frail elderly individuals. It renders a score which places the patients in one of three groups: normal nutritional status, at risk of malnutrition or malnourished [46, 47]. A clinically significant change is defined as a change in group classification. The patients in the intervention group are screened by a dietician at baseline and by a ward nurse or a dietician at the day of/day before surgery. The patients in the control group are screened by a study nurse at both measurements.*Medication safety*, polypharmacy and the use of potentially inappropriate medications is a growing issue in the elderly population. There is often a need of reviewing and altering an elderly individual’s prescribed medications to reduce the risk of adverse drug reactions and to enable beneficial pharmacological treatments [48–50]. The Safe Medication Assessment (SMA), including a review of the current list of medications [51], is used as a basis for assessing the individual patient’s medications in the trial. The instrument renders a score of 0–30, where a higher score indicates a safer treatment. A clinically significant change is defined as a shift of minimum 1 point in either direction. The questionnaire is filled out by a study nurse at baseline and at revisit, for all participants. To identify adverse drug reactions (ADRs), underuse of evidence-based drug therapy and effects of inappropriate medications, scoring scales [49, 50] and clinical judgements based on medical records will be used. These judgements will be retrospectively performed by senior clinicians [52].*Cognition*, a decline in cognitive function is naturally present in the ageing process. Some elderly individuals are experiencing a more pronounced decline, resulting in cognitive impairment or dementia [53]. In the trial, the Mini-Mental State Examination (MMSE) is used as a screening instrument of cognitive function at baseline. It is a validated and reliable assessment tool in screening for cognitive impairment [54]. The screening is performed by a study nurse at baseline for all participants, but the measurement is not done at follow-up.*Frailty* is an independent risk factor of adverse health outcomes and death [21] and also a predictor of increased hospital and health care costs [25]. The degree of frailty is assessed using the Clinical Frailty Scale (CFS-9). The scale ranges from 1, “very fit”, to 9, “terminally ill”. The scale has been validated and proven to be of prognostic value in clinical practice [26, 55, 56]. The estimates are performed by a study nurse at baseline and at revisit, for all participants. A clinically relevant change is defined as a shift of minimum 1 step on the scale. During the initial phase of the trial’s recruitment, a revision of the CFS-9 scale was made, including minor adjustments in the description of the different levels of frailty [57]. Before the updated version (v 2.0) was put into use, a new application to the Swedish Ethical Review Authority was made and was approved on 2021-05-31.*Complications*, postoperative complications are common in elderly patients undergoing colorectal cancer surgery. The complications can result in additional treatments, reoperations, the need of intensive care and death [7, 8]. The Clavien-Dindo classification is a validated and clinically relevant instrument for identifying and grading adverse postoperative events [58]. The postoperative complications are assessed by a physician based on data from the medical records at the time of revisit, for all participants.*Comorbidity*, the patient’s comorbidity is valued through the Charlson comorbidity index (CCI). The instrument is used to assess the total burden of disease and predicts a 10-year mortality for a patient, by using 19 categories of comorbidities. Each condition is given a grade of 1, 2, 3 or 6, based on the risk of death associated with the specific comorbidity [59, 60]. The CCI index estimate will be performed by a physician, based on data from the medical records at baseline and at revisit, for all participants.*Health-related quality of life (HRQoL)*. The instrument EuroQoL-5D-5L (EQ-5D-5L) is used to assess HRQoL in the trial. The tool consists of a questionnaire containing five health dimensions with five response levels and of a visual analogue scale (VAS) where the patient estimates their own overall current health. Each estimated score is represented by an index value which is derived from a pre-defined value set [61, 62]. The assessments are overseen by a study nurse at baseline and at follow-up (2 and 12 months), for all participants.*Health economical calculations*. A health care system perspective will be applied including hospital and primary care. Cost-effectiveness will be analysed based on mortality and HRQoL data (quality-adjusted life years [QALYs]) and costs of hospital care and primary care at baseline, 2 and 12 months post-surgery. An incremental cost-effectiveness ratio (ICER) is calculated regarding cost/QALY gained. QALYs are calculated by multiplying the health state value with the patient’s survival time at 12 months; see also the “Statistical methods for primary and secondary outcomes” section. Data regarding health care costs will be collected and documented for all participants at 2 months and 12 months from baseline. Hospital costs will be obtained from the Swedish Cost-per-Patient database [63] and from hospital-specific administrative systems. Primary health care costs will be collected from the administrative regional health care database in Västra Götalandregion (VEGA) [64] and by the use of models and actual health care contacts.*Mortality*, mortality data will be extracted from patient medical records and cross-checked against the Swedish Population Registry regarding all participants at 2, 3 and 12 months from baseline.

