## Assignment of interventions: blinding

### Who will be blinded {17a}

Neither participants nor caregivers are blinded to group assignment, as the intervention will be apparent. However, results will be analysed without knowledge of details of the groups.

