## Oversight and monitoring

### Composition of the coordinating Centre and trial steering committee {5d}

The trial has no separate steering committee, the trialists, [name] (principal investigator), [name] and [name], act as the steering committee.

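### The protocol contradicts itself on who assesses secondary outcomes; if its two tables govern, the assessor differs by arm for unblinded, judgement-dependent endpoints such as complications

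*Protocol article*

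**What the plan says.** All references are to the protocol article.

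- **Table 1 (intervention arm).** The study nurse row includes the Clavien-Dindo scale, timed as "Complications - Post-op visit". The section on comprehensive geriatric assessment and care lists the intervention team as "internal medicine physicians with geriatric profiling, study nurses, physiotherapists (and/or occupational therapists) and dieticians", so the study nurse is a role on the team that delivers the intervention.
- **Table 2 (control arm).** Clavien-Dindo and the Charlson index (CCI) are assigned to a "Member of the project steering groups". CFS-9, EQ-5D-5L, MMSE, SMA, ADL and MNA-SF are assigned to a ward or outpatient nurse.
- **Outcomes and measurements.** "The postoperative complications are assessed by a physician based on data from the medical records at the time of revisit, for all participants". CCI is also given to a physician working from records in both arms. A study nurse performs CFS-9, SMA and MMSE in every participant, and MNA-SF in controls.
- **Steering group.** "The trial has no separate steering committee"; the trialists fill that role (item 5d).
- **Blinding (items 17a and 17b).** "Neither participants nor caregivers are blinded to group assignment, as the intervention will be apparent". Only the analysis is to be masked to group. No masked outcome assessment is described.

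**The concern.** The three statements about complications cannot all be true. A steering group member may be a physician, so Table 2 can fit the outcome text. A study nurse who grades complications cannot.

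The Objectives section frames the secondary hypothesis in terms of complications, and Clavien-Dindo is a listed secondary endpoint. How many events are recorded depends partly on how thoroughly someone reads the chart and where they draw the line between grades. If each arm has its own unblinded grader, any difference in reading habit appears as a difference between arms. Masking the analyst does not help, because the difference is already in the data. Adjustment does not help either: no patient in one arm is graded by the other arm's assessor, so an assessor effect cannot be estimated separately.

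The same reasoning applies to follow-up CFS-9, SMA and ADL, all secondary endpoints for which the protocol counts a one-step or one-point shift as a relevant change.

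**Working it through.** **Step 1. Set the assignments side by side.**

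| Item | Table 1 (intervention) | Table 2 (control) | Outcome text | Consistent? |
|---|---|---|---|---|
| Clavien-Dindo | Study nurse | Steering group member | Physician, from records, both arms | No: Table 1 conflicts |
| CCI | Internal medicine physician | Steering group member | Physician, from records, both arms | Yes, if the member is a physician |
| CFS-9, SMA | Study nurse | Ward/outpatient nurse | Study nurse, both arms | No: Table 2 conflicts |
| MMSE (baseline only) | Study nurse | Ward/outpatient nurse | Study nurse, both arms | No: Table 2 conflicts |
| MNA-SF, controls | not applicable | Ward/outpatient nurse | Study nurse | No |
| ADL at follow-up | Study nurse | Ward/outpatient nurse | Physiotherapist or study nurse | Table 2 does not fit |

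EQ-5D-5L shows the same mismatch of roles, but the patient answers it and staff only oversee it, so an assessor effect is much less direct. MMSE and MNA-SF are not listed secondary endpoints; they matter here as evidence that the mismatch is not confined to one cell.

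**Step 2. Check whether the primary endpoint or the sample size is touched.** The only sample-size figure is 170 per arm for 90-day mortality, 15% versus 5%, 80% power, alpha 0.05, with 5% loss included. Two-sided, with mean proportion 0.10:

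n = [1.960·√(2·0.10·0.90) + 0.842·√(0.15·0.85 + 0.05·0.95)]² / 0.10² = 140.1

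With continuity correction: (140.1/4)·[1 + √(1 + 4/(140.1·0.10))]² = 159.5, rounded up to 160. Then 160/0.95 = 168.4, rounded up to 169, against the stated 170. The figure is reproduced. It rests on all-cause death, checked against the population registry, and does not depend on any grader.

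**Step 3. Illustrate what a grader difference could do.** The documents give no complication rate and no capture rates, so every input here except n is an assumption. Take a yes/no complication endpoint, the same true rate p in both arms, capture fractions a and b for the two graders, n = 170 per arm and a two-sided 5% test of two proportions.

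Spurious difference: d = p(a − b).

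False-positive rate: Φ[(d − 1.96·s0)/s1] + Φ[(−d − 1.96·s0)/s1], with s0 = √(2·m(1−m)/n), m the mean observed rate, and s1 = √{[p1(1−p1) + p2(1−p2)]/n}.

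Worked case, p = 0.40, a = 0.90, b = 0.80: observed rates 0.36 and 0.32, d = 0.04, m = 0.34, s0 = 0.0514, s1 = 0.0513. The two terms are about 0.119 and 0.003, giving 12.2%.

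| Capture a vs b | p = 30% | p = 40% | p = 50% |
|---|---|---|---|
| 90% vs 90% | 0 points, 5.0% | 0 points, 5.0% | 0 points, 5.0% |
| 90% vs 85% | 1.5 points, 6.1% | 2.0 points, 6.7% | 2.5 points, 7.5% |
| 90% vs 80% | 3 points, 9.7% | 4 points, 12.2% | 5 points, 15.4% |
| 90% vs 70% | 6 points, 25.3% | 8 points, 35.2% | 10 points, 46.9% |

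Each cell gives the spurious difference and the false-positive rate. With 161 per arm (170 less 5%), the 90% versus 80% row becomes 9.5% to 14.8%. The calculation does not say which arm would be favoured.

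**The case against.** The outcome text is the only place that describes how complications are graded: by a physician, from records, in both arms. If it governs, grading is not split by role, and Table 1 needs only a correction. The study nurse entry might mean recording the result on the CRF rather than grading it, and a ward nurse might act as study nurse for controls. The documents do not settle either point. This objection stands to the extent that differential grading is a risk, not an established feature of the trial.

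A reader might infer that the plan has fixed a different complication grader for each arm, so that the comparison is already confounded. The documents do not support that, because the outcome text says otherwise. Nor do they show the reverse: the article mentions separate CRFs for the two arms (item 18a) and an effort to keep the CGA team apart from control patients (Discussion), so arm-specific assessment is plausible in practice.

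A reader might also infer that CCI is scored inconsistently and so distorts the adjusted results. That goes too far. The CCI roles are compatible if the steering group member is a physician, and CCI is named as an adjuster only for the cost-effectiveness analysis, where adjustment is optional (item 20a).

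Finally, the capture rates above are chosen rather than observed, and a gap of 20 points between two chart readers is large.

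**Conclusion.** The contradiction is real and lies within the article itself. For complications, Table 1 cannot be reconciled with the outcome text if its entry means grading. For CFS-9, SMA, MMSE and control-arm MNA-SF, Table 2 departs from the text. If the tables govern, assessor and arm coincide for unblinded, judgement-dependent secondary endpoints, and no analysis can undo that.

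The size and direction of any bias cannot be derived from the documents. The illustration shows only that moderate differences in capture would matter: 5 points of capture barely moves the 5% error rate, while 10 points takes it to about 10–15%. Grading from records should limit the difference. All-cause 90-day mortality and the sample size are unaffected. This should be fixed; it does not undermine the trial's main conclusion.

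**What to change.** Correct Tables 1 and 2 so that they agree with the outcome text:

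- The same physician role grades Clavien-Dindo, and scores CCI, from medical records in both arms, masked to allocation where feasible. A grader outside the intervention team is preferable.
- One assessor role performs follow-up ADL, CFS-9 and SMA in both arms.
- Any charts already graded under arm-specific roles are regraded from records.

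The cost is some added chart review for the intervention arm, up to the planned 170 patients if these are currently graded by a nurse. When the article was written about 50 patients had been included across both arms, so regrading at that stage would have been a small task. Whether extra physician time is needed cannot be judged, because the article does not say who on the steering group is a physician.

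The contradiction does not require a new cut-off date or the grading of patients who miss follow-up. Item 18b says that, apart from a mortality check, non-attenders are not registered further, so grading them would be a separate change to the protocol.
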